### Trial withdrawal

A patient is withdrawn if they withdraw their consent or do not provide consent following randomisation.

### Trial interventions

#### Standard care physiotherapy (control)

The control group will receive physiotherapy care that is typically delivered in Australian hospitals^12^. This comprises of education (talk), early supervised ambulation (walk) once daily from the first postoperative day, and a single session of coached DB&C exercises (breathe) (Table 1).

##### Patient education—‘talk’

Patients will be educated on their risk of a PPC and slow recovery after surgery. They will be educated on the benefit of walking and breathing exercises to prevent complications and improve recovery after surgery [15, 16]. Following the first successful ambulation session, all participants will be strongly encouraged by their treating physiotherapist to sit upright, sit out of bed, walk away from their bedside (if safe to do so), or march on the spot beside their bed, as many times as they can during the following days to aid in the prevention of PPCs. They will be encouraged to seek assistance from a nurse if necessary and to walk with their visitors, or independently, once they are able to walk away from the bedside safely. Patients will be encouraged to perform the coached DB&C exercises independently every hour during the day until they are walking at least 5 min, four times a day. Patients will be provided with an information booklet containing all the supplied verbal information in written and pictorial format.

##### Early supervised ambulation—‘walk’

The standardised ambulation protocol [16, 17] (Table 2) will be provided as soon as practical after surgery by a physiotherapist. Patients will receive one supervised ambulation session per day until a threshold score is met [18] (Additional file 1), or discharge from hospital, whichever occurs first. At every session, the participant will be progressed sequentially through the protocol stages aiming to achieve a walking time of at least 10 min, but no more than 15 min, at an intensity of at least three on the Borg 10-point visual analogue scale (VAS) of perceived exertion [19], and where breathing is deeper than at rest. The treating physiotherapist will use a stopwatch to ensure the treatment session does not exceed 15 min and can provide a walking aid if clinically indicated. If necessary, ambulation sessions can comprise of equal work/rest intervals. Shorter, but not longer, rest times are allowable. The final achieved ambulation stage corresponds to total time walked, including the marching on the spot time, and not including rest periods.

**Table 2 Tab2:** ICEAGE ambulation protocol

Stage 1 (safety)	Sit over edge of bed/sit in chair minimum of 2 min
Stage 2 (safety)	March on spot 0–1 min
Stage 3 (ambulation)	March on spot/walk away from bedside 1–3 min
Stage 4 (ambulation)	March on spot/walk away from bedside 3–6 min
Stage 5 (ambulation)	Walk away from bedside 6–10 min
Stage 6 (ambulation)	Walk away from bedside 10–15 min
Stage 7 (ambulation)	Walk away from bedside > 15 min
Provide assisted early ambulation as soon as possible on the first postoperative day. At each session, progress through each stage in sequence. Time achieved in the session is accumulative. Aim to achieve rating of perceived exertion of greater than 3/10. Aim to assist patient to ambulate more than 10 min (stage 6 or greater). Once patient is able to ambulate past stage 3, patient can be assisted to ambulate with a physiotherapy assistant, as long as safe to do as determined by the ward physiotherapist. Interval training is permissible to obtain target walking time. Each interval of rest time must not exceed the preceding work time. Total session time is the accumulative work time. Provide assisted early ambulation once a day until discharged according to the discharge scoring tool.	

Successful ambulation is defined as continuously marching on the spot beside the bed or walking away from the bedside for more than 1 min. Time from surgery to time of first successful ambulation will be recorded. If participants are unavailable or unable to achieve ambulation for more than 1 min, the assisted ambulation session will be attempted once again on the same day. The reasons for participants being unable to ambulate or not achieving a minimum of 10 min will be recorded. If a participant is unable to participate in upright ambulation, then no other non-ambulatory exercises will be provided that day. All treating therapists will be provided with protocol badge cards and trained by the site investigator. An allied health assistant can deliver the ambulation protocol once this is deemed safe to do so by the treating physiotherapist. The professional qualification of the person assisting each ambulation session will be documented.

##### Coached respiratory exercises—‘breathe’

Participants will receive a single physiotherapy education and coached DB&C session within the first 2 days following surgery, or once the ward physiotherapist considers a patient cognitively capable of participation.

Physiotherapists will treat patients in upright sitting either in a bed or in a chair. The coached DB&C exercises will consist of two sets of 10 slow-flow breaths to maximum inspiratory capacity with two to three inspiratory sniff breath-stacking manoeuvres at the end of each deep breath followed by a 3- to 5-s breath hold [16, 17]. Each set of 10 breaths are followed by three coughs or forced expiratory technique with an open glottis called a ‘huff’, with a small firm pillow, or suitable substitute, pressed over on the abdominal incision to support the wound and encourage greater expiratory force. The treating physiotherapist will have the discretion to place hands on the patient’s chest wall during the coaching sessions to provide tactile feedback of performance. Total prescribed dosage of DB&C exercises is 20 breaths and six forced expiratory efforts every hour. No other prophylactic respiratory physiotherapy interventions or reminders to perform the taught DB&C exercises will be provided by the physiotherapist; this includes, but is not limited to, the following: manual or ventilator hyperinflation or recruitment manoeuvres in ventilated patients, manual techniques, positive expiratory pressure devices, or non-invasive ventilation.

Of note, all participants at Princess Alexandra Hospital and Northeast Health Wangaratta will be provided with an incentive spirometer by the nursing staff in the first 2 days after surgery as per routine nursing care at these hospitals. According to the pragmatic nature of this trial, this practice will continue and the incentive spirometer use will be recorded. Physiotherapists will not encourage incentive spirometer use in the control group.

#### Enhanced physiotherapy care (intervention)

The intervention group will receive the same care as the control group with the addition of the following (Table 1):

##### Patient education—‘talk more’

Education and an information booklet will be provided as per the control group [15, 16]. In addition, intervention group participants will receive extra reminders and prompts during the first five postoperative days to perform the prescribed rehabilitation and breathing exercises independently. Pragmatically, the number of additional education sessions and the use of exercise diaries and instruction sheets will be at the discretion of each treating physiotherapist based on their clinical experience and the individual needs of the participant.

##### Supervised early rehabilitation—‘exercise more’

Intervention participants will receive physiotherapist supervised early rehabilitation lasting at least 30 min provided at least once daily. Rehabilitation will consist of a combination of ambulation and non-ambulatory chair- or bed-based exercises (Fig. 2) starting as soon as possible after surgery and continuing daily thereafter for at least the next five postoperative days or until at least five daily sessions are delivered. Exercises will be provided in a top-down hierarchical sequence starting from ambulation and aiming for the maximum physical activity type the participant is able to attempt. Exercise delivery progresses sequentially down the protocol until at least 30 min of activity have been accumulated. For example, participants will first be assisted to ambulate for at least 15 min with a goal to achieve at least 30 min. If time ambulated is less than 30 min, the participant will attempt resistive lower limb exercises in standing for the remaining time or until fatigue limits the performance. If time still remains less than 30 min, participants will attempt upper limb/lower limb resistance exercises in sitting until fatigued. This process continues until a minimum total treatment time of 30 min has been reached. A treating physiotherapist is also permitted to prescribe a personalised training activity based on a detected functional deficit to be incorporated within the rehabilitation programme. These targeted and individualised sessions will be recorded.

**Fig. 2 Fig2:**
[figure not shown]
ICEAGE exercise protocol. reps repetitions

This early rehabilitation protocol has been designed so that critically unwell ICU patients can participate [20, 21]. A conscious, intubated, and ventilated patient could be assisted out of bed to march on the spot once assessed as safe [20, 21], and an unconscious patient could participate in 30 min of passive limb movement [22, 23] and/or functional electrical stimulation of major muscles [24]. The initial starting exercise for each rehabilitation session will be made pragmatically at the discretion of the treating physiotherapist using their own past experience and knowledge base regarding the participant’s current clinical and physiological status. No specific sedation score or assessment screening tool will be used to guide this decision.

Supervised activity in the intervention exercise protocol must aim to be continuous for more than 1 min, at an intensity of at least three on the Borg 10-point VAS of perceived exertion [18] and where breathing is deeper than at rest. The exception to this is for the passive limb exercises and functional electrical stimulation of muscles provided to unconscious or acutely unwell participants. Interval training is permitted; however, rest time cannot exceed the preceding active period. Once rest time becomes greater than the preceding work time, the exercise session is considered completed. The treating physiotherapist will use a stopwatch to ensure each rehabilitation session equals or exceeds 30 min. If a participant is unable to complete a 30-min session, the treating physiotherapist will document the reason. A further rehabilitation session later in the same day may be attempted to reach the 30-min threshold.

All sessions will be conducted by a physiotherapist until at least the fifth postoperative day unless the supervising physiotherapist is confident that a therapy assistant or the participant will undertake the rehabilitation programme exactly as prescribed for the minimum 30 min. After the fifth postoperative day, daily treatment with a physiotherapist or therapy assistant will continue until either a referral for sub-acute rehabilitation services is made (see endpoints), a participant is discharged from hospital, or once a threshold score is met [18] (Additional file 1), whichever occurs first. If the patient meets the discharge score prior to the fifth postoperative day, daily treatment will continue until the fifth postoperative day but cease thereafter.

##### Coached respiratory exercises—‘breathe more’

The mode, type, and timing of delivery of DB&C exercises will be provided as per the control group. Intervention group participants will receive at least three additional physiotherapist-coached DB&C sessions in the first two postoperative days. At least four sessions will be provided in total. The total number of sessions will be recorded. Beyond the second day, additional coached DB&C can be provided at the discretion of the treating physiotherapist if they consider the patient incapable of performing exercises unsupervised or requires additional respiratory exercises to prevent a PPC are indicated. Similar to the control group, no additional prophylactic respiratory interventions apart from the DB&C exercises will be provided.

#### Other components of postoperative care

Additional ambulation occasions or DB&C sessions conducted independently by the participant or assisted by other ward staff will not be measured nor controlled for as this would not be feasible or consistent with the pragmatic nature of this trial. All other aspects of patient care, including general anaesthesia, surgical techniques, intraoperative ventilation parameters, fluid delivery, prophylactic antibiotic prescription, pain management, use of lines and drains, general nursing care, and discharge planning, will be administered according to routine clinical practice at each participating centre.

The three participating sites have limited physiotherapy service on weekends and on public holidays. If protocol is unable to be delivered due to service limitations, this will be recorded.

#### Safety monitoring

Early rehabilitation of at least 30 min daily in ICU patents is safe when provided in consideration of the patient’s immediate clinical status and haemodynamic stability [25]. The emergency abdominal surgery population, in comparison, will be generally less acute. No adverse events in this population have been reported in similar exercise treatment protocols [26]. The following events will be reported if they occur during a treatment session and only if it is standard procedure at each site to monitor these parameters during physiotherapy treatment: symptomatic blood pressure or heart rate change 20% from resting, new cardiac arrhythmia, or drop in oxygen saturation > 10% from baseline, which fails to recover within 2 min of ceasing activity; patient requires increased sedation or inotropic support; line detachment; fall; or severe nausea. Adverse events will be immediately recorded in the participant’s medical record and in the case report form. The treating physiotherapist will immediately report the event to the site investigator who will alert the chief investigator within 24 h of the event for further investigation and classification. A significant adverse event (SAE) occurs where, in the opinion of the chief investigator, the event was directly related to the intervention or control treatments, was unexpected, and significantly impacted the participant’s immediate health and/or delayed recovery. All SAE will be reported to the ethics committee.

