### Ethics and dissemination

#### Retrospective consent

Ethics approval has been granted for eligible patients to be randomised prior to consent. Patients within the first two postoperative days after emergency abdominal surgery are often unwell and in an emotionally vulnerable state. Initial ethics approval was granted with a traditional enrolment into the trial following gaining of consent. However, following a planned interim analysis of trial conduct on the 50th patient recruited into the trial (unpublished data), patients and next of kin reported feeling distressed when approached by researchers in the first two postoperative days to discuss the trial. Further detailed feedback on the consenting process was sought from patients (*n* = 20) at 1-week post-surgery. All patients reported feeling too unwell in the first few days after surgery and disliked having to consider participating in a trial that was comparing two forms of low-risk commonly provided care. All patients indicated that they would prefer to provide retrospective consent. They recommended approximately no earlier than the third postoperative day or when they were not feeling nauseated. The two comparison interventions had nil documented occasions of harm at that point in the trial. Adverse events are similarly very low (< 1%) in critically unwell patients who are provided with 30 min of daily rehabilitation therapy [25]. There is minimal clinical risk to the patient being provided with either two arms of the study. Randomisation immediately on eligibility also allows the physiotherapy protocol to be delivered without delay, possibly enhancing the clinical outcome for all participants. Additionally, the primary outcome measure is non-invasive, has minimal risk, and requires no additional participation from the patient outside of standard care. An application to all responsible ethics committees was placed to alter consent to a retrospective consent following randomisation and was granted.

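### The listed adverse events count only inside treatment sessions, so events during encouraged unsupervised exercise have no stated reporting route and the counts are not comparable between arms

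*Protocol article*

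**What the plan says.** The Safety monitoring section of the protocol article sets two conditions for an event to be reported: "The following events will be reported if they occur during a treatment session and only if it is standard procedure at each site" to monitor the parameters during physiotherapy. One list then follows: symptomatic blood pressure or heart rate change, new arrhythmia, desaturation, escalation of sedation or inotropes, line detachment, fall and severe nausea. The route starts with the person giving the treatment: "The treating physiotherapist will immediately report the event to the site investigator". That person knows the allocation (Blinding).

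Part of the treatment takes place outside sessions. In both arms patients are urged to walk and do breathing exercises on their own (Patient education, 'talk'). The 'talk more' section goes further for one arm: "intervention group participants will receive extra reminders and prompts during the first five postoperative days to perform the prescribed rehabilitation and breathing exercises independently". Under Other components of postoperative care, extra walking or breathing sessions "conducted independently by the participant or assisted by other ward staff will not be measured nor controlled for", on the stated grounds of feasibility and pragmatism.

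Planned session time differs by arm. Trial design caps control at 15 minutes of supervised ambulation a day until a threshold score is met, and sets a minimum of 30 minutes a day for five days in the intervention arm. Protocol endpoints delays the threshold-score stop for the intervention arm during those five days.

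**The concern.** An adverse-event count is comparable between randomised arms when both are observed for the same time in the same way. Here the observation window is the treatment session, and session time is the very thing that differs by allocation. The same window leaves out the unsupervised activity that the enhanced package sets out to increase.

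A fall, a detached line or a new arrhythmia while a patient walks alone in response to a prompt is therefore not a reportable event under the rule. A low or zero count could mean that nothing happened, or that it happened outside a session. For the physiological items it could also mean that the site does not monitor them.

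At stake are the adverse-event review at the interim analysis (Trial monitoring) and any later statement about these events by arm. The article already reports, under Retrospective consent, that "The two comparison interventions had nil documented occasions of harm at that point in the trial". If the same rule applied then, that statement carries the same limits.

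**Working it through.** **The plan's own ratios.** Table 1, item 2b, aims for at least double the daily physical activity and at least four times the coached breathing in the first two days. The session rules reproduce both: 30/15 = 2 for daily exercise minutes, and 4/1 = 4 for coached breathing sessions.

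**Supervised exercise time over five days, with full delivery.**
- Intervention: 5 × 30 = 150 minutes or more.
- Control: 5 × 15 = 75 minutes or less. Ratio: 150/75 = 2.0 or more.
- Control stopped by the threshold score after day 3: 3 × 15 = 45 minutes. Ratio: 150/45 = 3.3.
- Control stopped after day 2: 2 × 15 = 30 minutes. Ratio: 150/30 = 5.0.

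**What this does to background events.** The documents give no event rate for this population, so the rates here are assumptions. Take an identical background rate λ per hour in both arms, unrelated to exercise, and 288/2 = 144 patients per arm. The expected number of patients with a recorded event is 144 × (1 − exp(−λ × supervised hours)), with 150/60 = 2.5 hours in the intervention arm.

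| Assumed λ per hour | Intervention, 2.5 h | Control, 1.25 h (5 days) | Ratio | Control, 0.75 h (3 days) | Ratio |
|---|---|---|---|---|---|
| 0.005 | 1.79 | 0.90 | 1.99 | 0.54 | 3.32 |
| 0.02 | 7.02 | 3.56 | 1.98 | 2.14 | 3.28 |
| 0.05 | 16.92 | 8.72 | 1.94 | 5.30 | 3.19 |

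Over a common calendar window the expected ratio would be 1. The session window turns no difference into a two- to three-fold excess.

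**The opposite direction.** Assume an in-session risk of 1% in each arm and an out-of-session risk of 4% in control and 8% in the intervention arm. The recorded ratio is 1/1 = 1.0. The ratio over all events is (1 + 8)/(1 + 4) = 9/5 = 1.8. Here the rule hides a real excess.

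**The site condition.** It sits before the colon that introduces the whole list, so as written it covers falls and line detachments as well as vital signs. Neither depends on monitoring a parameter. Within a site it applies to both arms alike, so its main effect is to lower and blur absolute rates by mixing unmeasured zeros with true ones.

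**What is collected elsewhere.** The secondary outcomes include mortality to one year, unplanned ICU admission, sepsis to day 7, prolonged ileus and patient-reported complications at 90 days, in both arms and regardless of sessions. None of them records an inpatient fall, a detached line or a transient arrhythmia as such.

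**The case against.** The strongest reply is that a higher count under more exercise may be a true effect. If exercise itself carries a risk per minute, twice the exercise causes more events, and a per-patient comparison by allocation rightly shows this. That stands: only events unrelated to exercise are inflated by the longer window. It does not rescue the rule, because in-session counts cannot separate the two kinds and out-of-session events are still lost.

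Other replies also stand in part. Unsupervised exercise is encouraged in both arms and only the extra prompting differs. The article states no formal between-arm analysis of adverse events. The site condition was probably meant for vital signs only; if so, the sentence needs correcting and the session limit remains.

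A reader might infer more than the documents support:
- *That the trial cannot say whether the package is safe.* The secondary outcomes listed above are collected in both arms outside sessions.
- *That the absence of a screening tool ("No specific sedation score or assessment screening tool will be used to guide this decision") contradicts the safety section.* The same text bases the starting exercise on the patient's current clinical and physiological status. The safety section restricts what is reported; it does not make clinical monitoring optional.
- *That the consent change rested on the nil-harm count.* It rested mainly on reported distress and on feedback from 20 patients. Nor can that count be set against the cited rate below 1% in critically unwell patients, whose unit the article does not give.

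**Conclusion.** The point holds as a defect in a stated rule. Recorded counts of the listed events will be incomplete, because events outside sessions have no stated route. They will not be comparable between arms, because supervised exercise time is at least 150 against at most 75 minutes over five days. The ratio of at least 2 assumes sessions delivered as planned; missed intervention sessions would reduce it and early control stops would raise it. The recorded ratios of about 1.9 to 3.3 for background events, and the masked 1.8, rest on assumed rates and only show that the distortion can go either way. The conclusion is confined to these listed events. It does not touch the primary outcome or the sample size. The change is worth making because the arms can be put on equal observation at small cost.

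**What to change.** In Safety monitoring, replace the session-only window for events that the medical record can show. The masked assessor would record falls, line detachment, new arrhythmia and increased sedation or inotrope need over the same calendar window in both arms, whether or not in a session. The window would run from randomisation to day 7, when daily assessment ends, or to day 14 or acute discharge where the record is already read for ileus and pneumonia. The assessor needs only the event and its date, which helps to preserve masking.

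Limit the site-monitoring condition to the physiological parameters and add a field for whether each was monitored (yes/no). Keep in-session events as a separate list, reported per patient and per session.

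The cost is a few case report form fields and an amended paragraph. More background ward events will be listed in both arms, and there is some extra record reading after day 7. Recruitment began in June 2015 and was expected to finish in late 2018, so participants already enrolled need retrospective record review or must be reported separately.

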## Abbreviations

CRF: Case report form
CXR: Chest X-ray
DB&C: Deep breathing and coughing
EQ-5D: EuroQual five domains
ICEAGE: Incidence of Complications following Emergency Abdominal surgery—Get Exercising
ICU: Intensive care unit
LOS: Length of stay
mILOA: Modified Iowa level of assistance
PPC: Postoperative pulmonary complication
PPOI: Prolonged postoperative ileus
QOL: Quality of life
SAE: Serious adverse event
SAQ: Self-administered physical activity questionnaire
SOFA: Sequential organ failure assessment
VAS: Visual analogue scale
WHODAS: World Health Organisation disability assessment score

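### SAE status, and with it ethics-committee reporting, requires relatedness, unexpectedness and significant impact together, while adverse events are captured only in sessions and under a site-dependent monitoring condition

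*Protocol article*

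**What the plan says.** The Safety monitoring section of the protocol article works in two tiers.

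**Capture.** Items on a fixed list "will be reported if they occur during a treatment session and only if it is standard procedure at each site to monitor these parameters". The list starts with physiological changes (blood pressure, heart rate, arrhythmia, saturation), adds a need for more sedation or inotropic support, and ends with "line detachment; fall; or severe nausea". Adverse events are entered at once in the medical record and case report form. The treating physiotherapist tells the site investigator immediately, and the chief investigator is alerted within 24 h to investigate and classify the event.

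**Classification.** The section introduces the term this way: "A significant adverse event (SAE) occurs where, in the opinion of the chief investigator". Three conditions must then hold jointly: "the event was directly related to the intervention or control treatments, was unexpected, and significantly impacted", with the impact being on short-term health or on the speed of recovery. All SAEs go to the ethics committee. The article states no external route for other events.

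The Abbreviations list expands the same acronym differently: "SAE: Serious adverse event".

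Two sections draw on the harm record. Trial monitoring includes adverse events among the topics of the interim review. Retrospective consent, describing the review at the 50th patient, says: "The two comparison interventions had nil documented occasions of harm at that point in the trial". That statement is one of several reasons given for randomising before consent.

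**The concern.** Seriousness, causality and expectedness answer different questions. Here they are joined in one test that rests on the chief investigator's opinion, and that test decides whether the ethics committee hears of an event. An event that badly hurts a participant and is plainly caused by a session fails the test if it is judged expected.

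The capture rule adds two limits. The same desaturation is reportable where saturation is routinely monitored during physiotherapy and not reportable where it is not. Events between sessions are off the list, although the trial encourages activity between sessions.

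At stake are the completeness of what the ethics committee sees and the weight that a statement of no documented harm can bear. The estimate of the primary outcome is not at stake.

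**Working it through.** The plan gives no harm rate of its own to reproduce, so most of the check is a reading of the text.

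**1. Follow an injurious fall in a session.** A fall is on the list. It is recorded in the medical record and case report form, goes to the site investigator, and reaches the chief investigator within 24 h. Only then does the SAE test apply. The fall is therefore documented; what can be lost is the SAE label and the ethics-committee report.

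**2. Count what the SAE test lets through.** Three yes/no conditions give 2 × 2 × 2 = 8 combinations, and only one (related, unexpected, significant) is an SAE. Of the 2 × 2 = 4 combinations with significant impact, three are not SAEs:

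| Directly related | Unexpected | SAE |
|---|---|---|
| yes | yes | yes |
| yes | no | no |
| no | yes | no |
| no | no | no |

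These are logical cases, not frequencies. The second row matters most: harm caused by trial treatment but judged expected.

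**3. Read the capture rule beside the trial's own instructions.**
- The condition "only if it is standard procedure at each site to monitor these parameters during physiotherapy treatment" precedes the whole list. It fits vital signs. Read literally it also covers falls and line detachment, which are not monitored parameters, so its reach is ambiguous there.
- The *talk* section urges all participants to walk as often as they can, with visitors or alone once safe. The *talk more* section adds prompts for independent exercise in the intervention arm. Other components of postoperative care says that independent ambulation is not measured. A fall during such walking lies outside the session window.

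**4. Ask what the nil-harm statement covers.** Trial monitoring speaks of adverse events and Retrospective consent of documented harm; neither says SAE. Because recording comes before classification, the SAE test does not reduce that count. The session-only window and the monitoring condition can reduce it.

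**5. Size of the nil-harm statement, for context.** Assume that it refers to 50 patients, counts patients with any harm, and that capture was complete.
- One-sided 95% upper limit: 1 − 0.05^(1/50) = 5.8%.
- Two-sided 95% upper limit: 1 − 0.025^(1/50) = 7.1%.
- Chance of seeing none in 50, (1 − p)^50: 61% at p = 1%, 36% at 2%, 8% at 5%.

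Incomplete capture weakens the statement further, by an amount that the article does not allow one to compute.

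**The case against.** The strongest defence is that recording and escalation are separate steps. Every listed in-session event is documented and reaches the chief investigator, so a narrow SAE label does not shrink the adverse-event count. Gross harm is visible elsewhere: mortality, unplanned ICU admission, sepsis and 90-day patient-reported complications are secondary outcomes whether or not they arise in a session. The section never calls the listed events expected. It also says that similar exercise protocols in this population reported no adverse events, which points towards treating such events as unexpected. The case report form and data dictionary are not shown, so separate fields for relatedness and expectedness may already exist. All of this stands, and it narrows the point.

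Three stronger readings are tempting, and the document supports none of them:
- *That an injurious fall in a session goes unreported.* It is listed and passed on before any SAE test. Only the ambiguous monitoring condition, read literally, could exclude it.
- *That the nil-harm statement rests on the SAE definition.* The wording refers to documented harm, no definition is given, and the interim data are unpublished.
- *That under-capture falls mainly on the intervention arm.* Planned supervised exercise over five days is at least 5 × 30 = 150 min against at most 5 × 15 = 75 min. But the capture rule is the same in both arms, the longer sessions lie inside the capture window, and the monitoring condition is tied to site. Equal hazard per minute would be an assumption: intervention time may include chair, bed or passive exercise, while control sessions are ambulation only.

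The defence does not answer the joint test for ethics-committee reporting, the site-dependent capture, or the two meanings of SAE.

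**Conclusion.** The point holds as one about safety reporting. As written, a harmful in-session event can escape ethics-committee reporting because it is judged expected or not directly related: three of the four logical cases with significant impact are not SAEs. Capture of physiological events depends on site routine, and falls during independent walking that the trial encourages are not captured as adverse events. The statement of no documented harm therefore covers a restricted set of events. Even with complete capture in 50 patients, it would be compatible with a per-patient rate of up to 5.8% (one-sided) or 7.1% (two-sided). Those limits assume that the statement covers 50 patients and counts patients.

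The protocol should be changed here, but the flaw does not touch the primary estimate and does not show that any harm was hidden. A reader might infer that the harm count is biased towards zero by the SAE definition. That does not follow, because the definition acts after events have been recorded.

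**What to change.** In Safety monitoring:
- Define a serious adverse event by its consequence for the participant alone.
- Record relatedness and expectedness as separate judgements.
- Report to the ethics committee every serious event that occurs during trial treatment or is attributed to it, whether or not it is judged expected.
- State that the site-monitoring condition applies only to physiological parameters and not to falls or line detachment, and record where a parameter was not monitored.
- Report harms by arm.
- Use one meaning of SAE: reconcile *significant* in this section with *serious* in the Abbreviations list.

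Where the absence of documented harm is cited under Retrospective consent, say which events and which time window it covers.

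The cost is protocol wording and, where the fields do not already exist, the case report form. The downsides are a few more reports to the ethics committee and possibly a less favourable harm count. Recruitment began in June 2015 and was expected to end in late 2018, so a change made during the trial would mix two capture rules; harms before and after it would have to be reported separately.
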